### Baseline assessment

After group allocation, all participants take part in a baseline assessment about demographic questions, alcohol use, actual medication, personality, and clinical symptoms (see Table 1). In addition, participants conduct the computer-based Incentive Conflict Task (ICT, [52]) during the baseline assessment.

### Neurofeedback setup

rtfMRI NFB is conducted at Siemens 3 T Tim Trio scanners (Siemens Healthineers, Erlangen, Germany) at the Central Institute of Mental Health in Mannheim, Germany. Each participant receives neurofeedback training on three scanning days within a period of two weeks. On each day a 5:21 min T1-weighted anatomical MPRAGE scan, a 12:00 min functional resting state scan with eyes closed, and three neurofeedback runs of 9:29 min are conducted. At the beginning of each session an MPRAGE image is acquired with a time of repetition (TR) of 2.3 s, an echo time (TE) of 3.03 ms, 9° flip angle, a field of view of 256 mm with 192 sagittal slice, a matrix size of 256 × 256 mm, 1x1x1 mm voxel size, and GRAPPA with iPAT = 2.

Resting state and NFB sessions are scanned with echo-planar imaging (EPI) sequences with a TR of 1.64 s, a TE of 30 ms, 73° flip angle, a field of view of 192 mm, 3x3x3 mm voxel size, 33 slices of 3 mm thickness with a distance factor of 33%, and GRAPPA with iPAT = 2.

During NFB scans, reconstructed DICOM images are transferred from the imaging computer to a laptop that preprocesses the images and extracts the neurofeedback signal by means of an in-house software. The feedback value is then send to a presentation computer and shown to the participant in the scanner as a thermometer value besides the picture of an alcoholic beverage preferred by the participant (beer, wine, or both). See Fig. 2 for an illustration. The thermometer is updated with every new volume. The order of pictures is randomized between participants.

**Fig. 2 Fig2:**
[figure not shown]
Real-time fMRI neurofeedback setup. Acquired images are reconstructed and send to a laptop running in-house MATLAB (MathWorks Inc., Sherborn, MA, USA) scripts based on SPM8 (Wellcome Department of Cognitive Neurology, London, UK) functions to preprocess the images and extract the neurofeedback signal. The feedback value is send to a computer running Presentation software (Neurobehavioral Systems, Inc., Albany, CA, USA) and presented to the participant in the scanner as a thermometer value besides a picture of an alcoholic beverage

rtfMRI NFB is conducted with in-house MATLAB (MathWorks Inc., Sherborn, MA, USA) scripts based on SPM8 functions (Wellcome Department of Cognitive Neurology, London, UK), and Presentation software (Neurobehavioral Systems, Inc., Albany, CA, USA) to present pictures and the feedback signal. On each scanning day, the acquired anatomical image is first segmented and normalized to MNI standard space. The inverse deformations of the normalization are then applied to warp the masks of the target regions into subject space.

During rtfMRI NFB scanning, functional images are realigned to the mean of the first 10 functional images and resliced. Then, the mask images are resampled to the space of the current image and mean intensity values from the voxels in the target regions are extracted.

For activation NFB, intensity values during presentation of alcohol images are averaged over the last three volumes (moving average) to stabilize the feedback signal and percent signal change with regard to the preceding fixation cross block is calculated. The scale of the feedback thermometer is adaptively adjusted to the maximum absolute signal change and the feedback signal is presented to the participant.

For connectivity NFB, partial correlations between the intensity values of the VS and right IFG adjusted for the cerebro-spinal fluid signal over the last 15 volumes are used to calculate the feedback signal. Again, the scale of the feedback thermometer is adaptively adjusted to the maximum absolute value reached. In this exploratory group, the goal of the intervention is to increase the inhibiting influence of the rIFG to the VS and the participants are instructed to downregulate the depicted process. However, a negative correlation between VS and rIFG could arise from the desired state, but also from an inverse behavior of the system with increased VS and diminished frontal activity. To enforce the top-down inhibitory state of the system we included the additional constraints in the connectivity feedback that the VS should be downregulated and the rIFG should be upregulated and switch negative feedback values to positive if these constraints are not met.

### Task design

NFB sessions have a block design with alternating presentation of a fixation cross (baseline; 41 s) and a picture of a preferred alcoholic beverage (beer, wine, or both; approx. 51 s), each for 6 times. Approximately 10 s after onset of the alcoholic pictures a feedback thermometer is shown on both sides of the picture and updated every TR (feedback; 41 s). On the first and third day, the last (third) run is conducted as a transfer run without presentation of the feedback signal (Fig. 3).

**Fig. 3 Fig3:**
[figure not shown]
Experimental design. Design of neurofeedback (left) and transfer (right) tasks. Each run consists of 6 repetitions of the displayed sequences. The last (third) runs on the first and third scanning day are conducted as transfer sessions without the neurofeedback signal. TR: Time of Repetition (1 TR = 1.64 s)

On each scanning day participants rate their craving on a visual analog scale directly before and after scanning. After completing the third MRI scanning session, participants are asked to answer alcohol-related questionnaires (see Table 1).

### Follow-up assessments

Follow-up assessments take place monthly after the last MRI session over a period of three months. At the first two time points participants are contacted by phone and asked about their current medication, their abuse of tobacco, nicotine and drugs and a potential alcohol relapse (see Table 1). Three months after the last MRI session, patients are invited to a final appointment at the CIMH. During this session, blood samples are collected and participants are asked about substance use and answer alcohol-related questionnaires (see Table 1). For the final appointment, patients receive a monetary compensation of 50 €.

### Statistical analyses

As primary outcome analysis we will conduct group comparisons of relapse rates with survival analysis and assess reduction of alcohol intake during the follow-up phase. As secondary and exploratory outcome measures we will assess whether rtfMRI NFB reduces alcohol craving during the NFB sessions, how brain activation and brain connectivity changes within and between the sessions, whether functional or structural MRI markers can be identified that predict neurofeedback learning and the success of the intervention, and whether differences in efficacy of the group-specific interventions do exist.

To analyze the effects of rtfMRI NFB, offline data analysis will be conducted with MATLAB and SPM. Data preprocessing will consist of slice-time correction, realignment, segmentation of the anatomical image, normalization to the MNI space, smoothing, and identification of outlier volumes with excessive head motion. The preprocessed data will be used in first level single subject analyses in which the time courses of the experimental conditions will be convolved with the canonical hemodynamic response function and used in a general linear model to estimate brain responses during rtfMRI NFB. Then, first level results will be used in second level group comparisons to estimate differential activation between groups, test for associations with clinical variables, and assess the predictive value of imaging markers for the future course of the disease. Additionally, large-scale adaptations in functional networks during rtfMRI NFB will be assessed by whole-brain psychophysiological interaction analysis [53].

Depending on the type of the data, missing data will either be left out from the analyses (e.g. fMRI data), or imputed (e.g. missing questionnaire items).

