**Methods:**

*N* = 100 patients with Alcohol Use Disorder will be randomized to 5 parallel groups in a single-blind fashion and receive real-time functional magnetic resonance imaging neurofeedback while they are presented pictures of alcoholic beverages. The groups will either downregulate the ventral striatum, upregulate the right inferior frontal gyrus, negatively modulate the connectivity between these regions, upregulate, or downregulate the auditory cortex as a control region. After receiving 3 sessions of neurofeedback training within a maximum of 2 weeks, participants will be followed up monthly for a period of 3 months and relapse rates will be assessed as the primary outcome measure.

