### Power calculations

Power calculations were conducted with the G*Power software package [54]. In the clinical analysis (follow-up measures) the power for detecting group differences at *p* < .05 under the assumption of a medium effect size (Cohen’s d = .5) is 78% with two sample *t*-tests when treatment (*n* = 60) and control groups (*n* = 40) are pooled. Assuming an effect size of f = .61 as observed for the neurofeedback effect on VS reduction in our pilot study [18], the neurofeedback analyses based on an ANOVA repeated measures model with a group x time contrast has a power of 89% in the VS and of 88% in the rIFG to detect FWE (Bonferroni) corrected significant results in the respective ROI analyses.

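### The only clinical power figure (78%) is for a t-test on a mean difference and does not apply to the survival comparison of relapse named as primary

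*Protocol article*

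**What the plan says.** The Methods part of the Abstract names a single primary outcome: "relapse rates will be assessed as the primary outcome measure". The section Statistical analyses describes the primary outcome analysis in one sentence with two parts. The first is "we will conduct group comparisons of relapse rates with survival analysis"; the second is an assessment of reduced alcohol intake over follow-up.

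The section Power calculations gives one figure for the clinical follow-up measures. The effect is d = 0.5, the level is p < .05, and the power "is 78% with two sample *t*-tests when treatment (*n* = 60) and control groups (*n* = 40) are pooled". Whether the test is one-sided or two-sided is not stated. No control relapse rate, expected number of relapses, HR or dropout rate appears there. The remaining figures in that section concern the neurofeedback imaging analyses.

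**The concern.** A two-sample t-test compares means, and its power depends on the standardised mean difference and the group sizes. A log-rank or proportional-hazards comparison of relapse depends on the number of relapses and the HR. A value of d fixes neither. The printed power therefore belongs to a different test from the one that the article names for relapse.

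If the relapse comparison turns out null, readers will set it against a claimed 78% power, without knowing which reduction in relapse the trial could have detected or excluded.

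**Working it through.** **1. Reproducing the stated 78%.** Inputs from Power calculations: d = 0.5, n = 60 and 40, alpha 0.05. The noncentrality parameter is 0.5 × √(60 × 40 / 100) = 2.449, with 98 degrees of freedom.

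- One-sided t-test: 78.5%. This matches the stated figure.
- Two-sided t-test: 67.9%. This does not match. A two-sided test would need d of about 0.565 for 78%.

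**2. What the same d could mean for relapse (illustration).** The 3-month control relapse rate is not given. As an assumption I use 57-75%, the complement of the 25-43% abstinence in the Background. That figure carries no follow-up period and is not used there as a design input. The formulas are:

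- odds ratio = exp(d × π/√3) = exp(0.5 × 1.814) = 2.48
- treated relapse pt: odds(pt) = odds(pc) / 2.48, where pc is control relapse
- HR = ln(1 − pt) / ln(1 − pc)
- relapses = 60 pt + 40 pc
- Schoenfeld: z = |ln HR| × √(relapses × 0.6 × 0.4); power = Φ(z − 1.960) two-sided, Φ(z − 1.645) one-sided

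| Control relapse | Treated relapse | HR | Relapses | Two-sided | One-sided |
|---|---|---|---|---|---|
| 57% | 34.9% | 0.508 | 43.7 | 59.3% | 70.9% |
| 60% | 37.7% | 0.517 | 46.6 | 59.8% | 71.3% |
| 66% | 43.9% | 0.536 | 52.8 | 60.1% | 71.6% |
| 75% | 54.8% | 0.572 | 62.9 | 58.2% | 69.9% |

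Like for like, the t-test exceeds the survival comparison by 78.5 − 71.6 = 6.9 to 78.5 − 69.9 = 8.6 points one-sided, and by 67.9 − 60.1 = 7.8 to 67.9 − 58.2 = 9.7 points two-sided.

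**3. Sensitivity to the conversion of d**, over the same control relapse of 57-75%:

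| Conversion | Two-sided | One-sided |
|---|---|---|
| Probit shift of 0.5 | about 50% | 62-63% |
| Cohen's h = 0.5 | 69-71% | 79-81% |
| ln HR = −0.5 | 39-50% | 51-62% |
| ln HR = −0.5 × π/√6 | 55-69% | 67-79% |
| Equal probability of superiority | 47-60% | 59-71% |

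The range over all conversions, including the logistic one, is about 39-71% two-sided and 51-81% one-sided. Using the odds ratio directly as a hazard ratio (HR = 1/2.48 = 0.40) would give 80-91% two-sided. I leave it out of the range because the two measures differ materially when relapse is this common.

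**4. Detectable HR, without any conversion of d.** HR = exp(−(z_alpha + 0.772) / √(relapses × 0.24)), where 0.772 is the normal quantile for 78% power.

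- 60 relapses: two-sided exp(−2.732/3.795) = 0.49; one-sided exp(−2.417/3.795) = 0.53.
- 40 relapses: two-sided exp(−2.732/3.098) = 0.41; one-sided exp(−2.417/3.098) = 0.46.

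For a true HR of 0.7, two-sided power is 24% at 60% control relapse (52.4 relapses) and 28% at 70% (62.2 relapses).

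None of these figures allows for dropout, which would lower them.

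**The case against.** - **The t-test may be meant for alcohol intake.** The primary sentence has a second part, reduction of intake, for which a t-test could be suitable, and Power calculations refers to follow-up measures in general. This stands: the 78% need not be irrelevant to everything under the primary heading. It does not rescue relapse, which the Abstract names alone as the primary outcome and which has no other power statement.
- **The loss may look larger than it is.** A reader might set 78% against 58-60% and conclude that survival analysis costs about 20 points. The documents do not support that: the 78% is one-sided and the 58-60% two-sided, so about half of the gap is sidedness.
- **The illustrative figure is soft.** It needs a borrowed relapse rate and a chosen conversion, and no document fixes either. Reading a medium effect as Cohen's h gives 79-81% one-sided, no worse than the stated figure. This also stands, so 58-60% cannot be reported as the trial's power. Equally, the width of the range shows that d = 0.5 does not define an effect on relapse.
- **A condensed article may leave event assumptions to the full protocol.** That would excuse silence. It does not excuse printing, as the only clinical power figure, one that belongs to a different test. Still, the flaw is in the justification: it neither biases the result nor alters the conduct of the trial.

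**Conclusion.** The point holds for the relapse comparison. The 78% is the power of a one-sided two-sample t-test at d = 0.5; two-sided it is 67.9%. It is not the power of the survival analysis of relapse, for which the article gives no relapse rate, event count or HR.

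The mismatch itself needs no assumption; its size does. With control relapse of 57-75%, a logistic conversion of d, proportional hazards and no dropout, HR is about 0.51-0.57 with 44-63 relapses. Power is then about 58-60% two-sided or 70-72% one-sided, some 7-10 points below the t-test on the same convention. A reader might infer that the trial has 58-60% power for its primary outcome. The documents do not fix enough to say so.

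**What to change.** For relapse, replace the t-test figure with an event-based statement for the pooled 60:40 comparison. It should give the assumed 3-month control relapse with its source, the expected number of relapses, the sidedness of the test, and the HR detectable at that count. For example: with 60 relapses, 78% power requires an HR of about 0.49 two-sided (0.53 one-sided); with 40 relapses, about 0.41 (0.46).

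Keep the d = 0.5 figure only for the alcohol-intake comparison, labelled as such and with its sidedness stated: 78% one-sided, 68% two-sided.

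The cost is a rewritten power paragraph and a less favourable stated figure. Sample size, data collection and the planned analyses are unchanged.

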**Discussion:**

The results of this study will provide insights into the efficacy of real-time functional magnetic resonance imaging neurofeedback training in the treatment of Alcohol Use Disorder as well as in the involved brain systems. This might help to identify predictors of successful neurofeedback treatment which could potentially be useful in developing personalized treatment approaches.

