## Methods/Design

To investigate the effect of rtfMRI NFB and identify the underlying neural mechanisms we will include *N* = 100 patients with a diagnosis of alcohol use disorder recruited from the outpatient and inpatient clinics of the Department of Addiction Behavior and Addiction Medicine at the Central Institute of Mental Health (CIMH), Mannheim, Germany. Participants will be randomly assigned to one of 5 parallel groups. All groups will receive true rtfMRI NFB from different brain processes and will be followed up monthly for three months (Fig. 1).

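### The predictive value of imaging markers is assigned to second-level models in the trial's single sample; these give association and can overstate performance in new patients

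*Protocol article*

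**What the plan says.** The article describes a single sample: "100 patients with a diagnosis of alcohol use disorder recruited from the outpatient and inpatient clinics" (Methods/Design), allocated to five parallel groups. No second cohort is mentioned.

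The Statistical analyses section opens the list that contains the marker aim with "As secondary and exploratory outcome measures we will assess". One item is "whether functional or structural MRI markers can be identified that predict neurofeedback learning and the success of the intervention", so at least some markers are to be found in this study. The method follows in the next paragraph: "Then, first level results will be used in second level group comparisons to estimate differential activation between groups". The same sentence adds two further uses of these models: testing associations with clinical variables, and a task to "assess the predictive value of imaging markers for the future course of the disease". Association and predictive value are thus listed as separate goals but given to one type of model.

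The abstract's Discussion states the intended use: "This might help to identify predictors of successful neurofeedback treatment which could potentially be useful in developing personalized treatment approaches". The closing paragraph of the main Discussion says much the same.

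**The concern.** A second-level group model relates first-level maps to a group or clinical variable across the patients in the data. What it returns is the strength of association in those patients. Predictive value is a different quantity: how well a rule fixed in advance performs in patients who did not help to build it.

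The gap widens when the marker is chosen in the same data. A marker is then reported because its observed association was large, and part of that size is chance. Family-wise correction limits how often a null marker is reported. It does not shrink the effect of a marker that passes, and a stricter threshold raises the observed correlation needed to be reported at all.

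What is at stake is the claim about personalised treatment. It depends on performance in new patients, and the named method does not estimate that.

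**Working it through.** **The plan's own figure.** There is none on this point. The Power calculations section covers the pooled clinical comparison and the neurofeedback analyses in the ventral striatum (VS) and right inferior frontal gyrus (rIFG).

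**Inputs.** From the article: n = 100 in total; 60 when the three experimental groups are pooled (Power calculations); 20 per group if the split is equal. Assumed, because the article gives neither: the number of independent comparisons V and the true correlation r.

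**Check 1: markers reported after Bonferroni correction.**

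1. Critical correlation: r_c = t / √(n − 2 + t²), with t the upper .025/V quantile on n − 2 df.
   - V = 200, n = 100: t = 3.80, r_c = 3.80/√(98 + 14.4) = .358.
   - V = 200, n = 60: t = 3.90, r_c = 3.90/√(58 + 15.2) = .456.
2. Observed r on the Fisher scale: z ~ N(atanh r, 1/(n − 3)). For n = 100 and r = .20 the mean is .203, the SD 1/√97 = .1015, and the threshold atanh(.358) = .375.
3. Chance of passing: (.375 − .203)/.1015 = 1.69, so about 4.5%.
4. Mean observed r among markers that pass: .394. Overstatement of explained variance = .394²/.20² = .155/.04 = 3.9.

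The same steps for other inputs, by simulation on the Fisher scale:

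| n | V | true r | overstatement of explained variance |
|---|---|---|---|
| 100 | 200 | .20 | 3.9 |
| 100 | 200 | .30 | 1.9 |
| 100 | 200 | .40 | 1.2 |
| 100 | 200 | .50 | 1.02 |
| 100 | 2 | .20 | 2.1 |
| 100 | 2 | .30 | 1.2 |
| 100 | 2 | .40 | 1.0 |
| 60 | 200 | .20 | 6.0 |
| 20 | 10 | .30 | 4.8 |
| 20 | 10 | .50 | 1.9 |

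The large ratios belong to markers that seldom pass: at V = 200 and r = .20, 4.5% of the time at n = 100 and 1.4% at n = 60. At n = 100 and r = .50, 96% pass, with almost no overstatement.

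**Check 2: the strongest of m candidates is taken without a threshold.** Independent candidates, at most one of them true, continuous outcome, n = 100, 200 replicates per row. The last column repeats the selection inside each fold of a 10-fold cross-validation.

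| m | true r | R² in same patients | true R² of chosen marker | cross-validated R² |
|---|---|---|---|---|
| 2 | .30 | .105 | .087 | .060 |
| 100 | .30 | .107 | .050 | −.030 |
| 500 | .30 | .126 | .037 | −.074 |
| 500 | .50 | .261 | .249 | .211 |
| 500 | no true marker | .102 | 0 | −.137 |

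The two checks use different selection rules, so their ratios are not interchangeable. Both show little overstatement for a strong marker and a marked one for a weak marker in a wide search. In Check 2, cross-validation exposes the case with no real marker, which the same-patient R² does not. Correlated voxels would lower the effective number of comparisons.

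**The case against.** The strongest reply is that this is a condensed article. It states no selection rule, candidate count, prediction metric or validation scheme, and such details of an exploratory analysis are commonly left to an analysis plan that is not shown. That stands against any complaint that cross-validation is merely absent. It does not answer the narrower point: the article names a method for predictive value, and that method yields association.

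The search may also be narrow. The Power calculations describe Bonferroni-corrected analyses in VS and rIFG, and the Discussion gives a prior hypothesis that patients with marked ventral striatal cue reactivity before the intervention will benefit most. A marker fixed in advance needs no search. This stands as a limit on the size. It is not decisive, because the Discussion also stresses whole-brain coverage and regions that were not targeted.

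A reader might infer that the plan commits itself to selecting and evaluating markers in the same patients, or that prediction will be overstated several-fold. The article supports neither. Re-use of patients is an inference from the single sample and the named model. The multiple depends on V and r, which the article does not give. Nor will every surviving marker look far better than it is; a strong one is hardly inflated.

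Finally, the aim is exploratory and the wording about personalised treatment is hedged. That stands, and it limits the weight of the point.

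**Conclusion.** The point holds in a limited form. Followed as written, the Statistical analyses section would report in-sample association as predictive value. If markers are also identified in these patients, the reported strength can overstate performance in new ones. At n = 100 the overstatement of explained variance runs from about 1.0-fold (true r about .50) to about 4-fold (true r = .20, 200 independent comparisons, Bonferroni correction). It is larger in subsets, for example about 6-fold at n = 60 under the latter assumptions. These sizes illustrate the range under assumed inputs and are not forecasts for this trial. The primary relapse analysis, the randomisation and the data collection are not affected.

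**What to change.** Describe the second-level results as association only. Define predictive value as out-of-sample performance, estimated by cross-validation with any marker selection repeated inside each training fold. Use a metric suited to each outcome, for example a concordance index for time to relapse and out-of-fold R² for neurofeedback learning. In each case report the gain over a model with the T0 clinical variables alone.

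The cost is a little more analysis work on data already planned. The downside is a predictive figure that will usually be lower and less precise. With 100 patients it may be close to zero or negative for weak markers, as the cross-validated column in Check 2 shows.

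### Run as a classical repeated-measures ANOVA with missing fMRI data left out, the secondary VS and rIFG analyses lose every patient with a wholly unusable session; a mixed model would keep them and regain part of the lost information

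*Protocol article*

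**What the plan says.** The missing-data rule is one sentence in Statistical analyses: "missing data will either be left out from the analyses (e.g. fMRI data), or imputed". Imputation is illustrated with questionnaire items and leaving out with fMRI data. The sentence does not say whether a volume, a run, a session or a whole patient is left out. Preprocessing in the same section includes "identification of outlier volumes with excessive head motion".

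The longitudinal model is named only under Power calculations, which speaks of "neurofeedback analyses based on an ANOVA repeated measures model with a group x time contrast". The power claimed is 89% for the ventral striatum (VS) and 88% for the right inferior frontal gyrus (rIFG). It rests on f = .61 from the pilot study and refers to "FWE (Bonferroni) corrected significant results in the respective ROI analyses". No allowance for lost sessions is mentioned.

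On the schedule, Neurofeedback setup states: "Each participant receives neurofeedback training on three scanning days within a period of two weeks". Each day has three runs. Under Task design, "On the first and third day, the last (third) run is conducted as a transfer run without presentation of the feedback signal".

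**The concern.** Each statement is unremarkable alone; the difficulty lies in combining them. A classical repeated-measures ANOVA works on complete rows. If a session is left out, that patient contributes nothing to the group by time contrast, although the other sessions were scanned and are usable.

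Two things are at stake:

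- **Power.** With five groups and 100 patients, a group has about 20 patients if allocation is equal, so small losses matter.
- **Validity.** Patients enter after 5 to 21 days of controlled abstinence and must attend three scanning days within two weeks. A session may be missed after a relapse or spoiled by head motion, and either could be related to how well the patient learns to regulate the signal. Complete-case ANOVA is unbiased only if missing sessions are unrelated to the response. A likelihood-based mixed model needs only that they are missing at random given the observed sessions.

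**Working it through.** **Inputs from the article.** f = .61; stated power 89% and 88%; Bonferroni correction with the number of tests not given; three scanning days; transfer runs on two of them; N = 100 in five groups. Not given: the rate of unusable sessions, the within-patient correlation r, the number of time points in the contrast, and which groups are compared. These are assumed below.

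**Step 1: the plan's own power.** Take two groups of 20 (N = 40, k = 2), two time points (m = 2) and alpha = .05/3 = .0167. With noncentrality f²(N − k)(m − 1):

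- .61² × 38 = .3721 × 38 = 14.14
- critical F on 1 and 38 df = 6.27
- power = 88.9%

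This matches the stated 89% but is not the only match. Noncentrality f²N(m − 1) with alpha .05/4 gives 88.5%. G*Power's default noncentrality gives at least 96% for every design tried at alpha .001 or above. The stated figure is therefore neither confirmed nor refuted, and the configuration above is only one possible anchor.

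**Step 2: patients without complete data.** If each session is lost independently with probability q, the incomplete share over T sessions is 1 − (1 − q)^T.

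| q | Three sessions | 20 per arm becomes | Two sessions | 40 in total becomes |
|---|---|---|---|---|
| 5% | 14% | 17.1 | 10% | 36.1 |
| 10% | 27% | 14.6 | 19% | 32.4 |
| 15% | 39% | 12.3 | 28% | 28.9 |

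**Step 3: complete-case power.** The anchor has two time points, so the two-session losses apply. The formula of Step 1 gives:

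- N = 36: .3721 × 34 = 12.65, power 84%
- N = 32: .3721 × 30 = 11.16, power 78%
- N = 29: .3721 × 27 = 10.05, power 73%

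A second calculation fixed full-data power at 89% with alpha .025. Power fell to about 84-85%, 78-80% and 70-74% when 10%, 20% and 30% of patients were lost.

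**Step 4: what a mixed model regains.** Assume equal correlation r between sessions and independent loss, and write p = 1 − q. The information on the last-minus-first contrast, relative to full data, is:

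- three sessions: p³ + p²q(2 + r)/(1 + r) + pq²(1 − r), against p³ for complete cases
- two sessions: p² + pq(1 − r), against p² for complete cases

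For three sessions with q = .10 and r = .5: .729 + .081 × 2.5/1.5 + .009 × .5 = .869. The share of lost information regained is (.869 − .729)/(1 − .729) = 51%. Over q = 5-15% and r = .3-.7 the share runs from 46% to 57%.

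For two sessions the share simplifies to p(1 − r)/(1 + p). With the same q and r it is .9 × .5/1.9 = 24%, and over the same ranges it runs from 14% to 34%.

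The pattern of loss matters. As shares of lost power, with 10-30% of patients affected and r = .3-.7:

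| Pattern | Share of lost power regained |
|---|---|
| One random session of three missing | 56-68% |
| Session 2 missing, day 3 minus day 1 | 98-99% |
| Session 3 missing, day 3 minus day 1 | 31-40% |
| Patient stops after session 1 or 2 | 24-49% |
| Two time points, later one missing | 13-41% |

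For example, with 20% of patients affected, r = .5 and full-data power of 89%, complete cases give about 80%. The mixed model gives 85.6% for a random missing session and 82.9% for early stopping.

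**The case against.** The strongest objection is that the article does not prescribe listwise deletion. A reader might infer that the plan drops every patient with any bad scan, but the text does not support that. The unit left out is not stated, and the ANOVA appears only as the basis of a power calculation. Statistical analyses describes first-level models and second-level group comparisons without naming a repeated-measures model. Each day has three runs, so one spoiled run need not cost a session. The finer rules may also sit in a full protocol or analysis plan that is not shown. All of this stands, and it makes the point conditional. What remains is that the only longitudinal model named for these analyses does not tolerate a missing time point, and the stated rule for fMRI data is to leave it out. The transfer runs are more exposed than the training runs, since there is one per day on two days.

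A reader might also infer that a mixed model restores most of the lost power. It does not do so in general. Under early stopping, the pattern most plausible if relapse drives the loss, less than half comes back.

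A third tempting step is to apply the 27% loss over three sessions to the two-time-point power calculation, which gives 29 patients and 73% at 10% loss per session. That mixes two designs. Two time points at 10% leave about 32 patients and 78%; the 73% belongs to 15% loss per session.

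Finally, these outcomes are secondary and exploratory. That is correct and limits the weight of the point.

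**Conclusion.** The concern holds in conditional form. If the ROI analyses are run as a classical repeated-measures ANOVA with missing fMRI data left out, a patient with a wholly missing or unusable session drops out of the contrast. Power then falls below the stated 88-89%. In the anchor configuration it falls to 84%, 78% or 73% at 5%, 10% or 15% loss per session. The loss rates, their independence, the correlation and the configuration are assumptions, because the article gives none of them.

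A mixed model on the same data is the better choice. It gained over complete-case analysis in every missing-session pattern examined. The gain is partial: roughly half of the lost information for three sessions under independent loss, and less for two time points or when patients stop early. The argument from the weaker missing-at-random assumption does not depend on any of these power figures. Nothing here touches the primary relapse analysis.

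**What to change.** For the VS and rIFG ROI analyses, specify a linear mixed model fitted by REML to first-level contrast values per session. Include fixed effects for group, session and group by session, and a within-patient covariance (a random patient effect or an unstructured matrix). Include every usable session of each randomised patient. State the unit at which fMRI data are left out: volume, run or session. Keep the complete-case repeated-measures ANOVA as a sensitivity analysis.

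The change is to analysis wording only and needs no new data, patients or procedures. The small cost is exporting ROI values to a statistics package and choosing the covariance structure.
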